### Outcome Measures

SEIB consists of a complex intervention [45], designed to tailor both individual and family needs, that is expected to entail several interacting components and outcomes. Considering the relevance of SEIB’s intervention components in the almost immediate aftermath of a potential traumatic loss, we anticipate the primary outcome of SEIB refers to traumatic stress symptoms of both parents/children. The secondary outcomes of SEIB may refer to the individual level of complicated grief, psychological wellbeing, daily functioning, and social support in parents and children, while tertiary outcomes possibly refer to the parenting/family level and include parental capacity, parenting practices, and family functioning.

Given SEIB's initial focus on the potential misconceptions/maladaptive appraisals that usually follow a sudden death, and the early provision of trauma-reducing self-help methods, it is foreseen that SEIB may reduce traumatic stress symptoms of both parents/children. The reduction of this symptomatology may favor psychological wellbeing and optimize daily functioning, which in turn may strengthen the individual sense of self-efficacy and the ability to use the support from others within the social network, minimizing the chances for complicated grief. For the surviving parent, these conditions may set the stage for a more resourceful, stable, and organized parent more considerate of the child’s needs. Enhanced emotional availability in parents, combined with SEIB’s family perspective, may ultimately improve family functioning. Textboxes 2 and Textboxes 3outline the parent and child self-report measures that will be used.

The parent self-report measures.Impact of Event Scale-Revised (IES-R) [46] – assesses the subjective distress following a traumatic event. It is composed of 22 items rated on a 5 -point scale ranging from ‘not at all’ (0) to ‘extremely’ (4).Inventory of Complicated Grief (ICG-19) [47] – assesses the severity of complicated grief symptoms. It is composed of 19 items rated on a 5 -point scale ranging from ‘never’ (0) to ‘always’ (4).General Health Questionnaire (GHQ-12) [48] – assesses general psychological wellbeing. It is composed of 12 items rated on a 4 -point scale. Items indicating health range from ‘more than usual’ (0) to ‘much less than usual’ (3), and items indicating illness range from ‘not at all’ (0) to ‘much more than usual’ (3).Work and Social Adjustment Scale (WSAS) [49] – assesses functional impairment at work, home, and social life. It is composed of 5 items rated on a 9 -point scale ranging from ‘not at all’ (0) to ‘very severely’ (8).Crisis Support Scale (CSS) [50] – assesses perceived and received support after the occurrence of a crisis event. It is composed of 7 items rated on a 7 -point scale ranging from ‘never’ (1) to ‘always’ (7).Parenting Coping Scale (PCS) [51] – assesses general parental ability to cope with the role of parenting. It is a brief single -item composed of 5 statements, forming a 5 -point scale rated from ‘coping very poorly’ (1) to ‘coping very well’ (5).Alabama Parenting Questionnaire (APQ) [52] – assesses several dimensions of parenting. A total of 14 items referring to parental involvement (7 items) and parental discipline (7 items) will be used and rated on a 5-point scale ranging from ‘never’(1) to ‘always’ (5).Family Assessment Device (FAD) [53] – assesses family climate and functioning. The General Functioning Scale is one of its subscales and the one that will be used. It focuses on family (un)healthy functioning and it is composed of 12 items rated on a 4-point scale ranging from ‘strongly disagree’ (1) to ‘strongly agree’ (4).

: The child self-report measuresChildren’s Impact of Event Scale (CRIES-8) [54] – assesses the subjective distress following a traumatic event. It is composed of 8 items rated on a 4-point scale ranging from ‘not at all’ (0) to ‘often’ (5).Inventory of Prolonged Grief for Adolescents (IPG-A) [55] – assesses symptoms of prolonged grief disorder. It is composed of 30 items rated on a 3-point scale ranging from ‘almost never’ (1) to ‘always’ (3).Strengths and Difficulties Questionnaire (SDQ) [56] – assesses psychological adjustment in children and adolescents. It is composed of 25 items rated in a 3-point scale ranging from ‘not true’ (0) to ‘certainly true’ (2), and an impact supplement focusing on functional impairment.Alabama Parenting Questionnaire (APQ) [52] – encloses a parent and child version. The equivalent items of the parent version will be used in the child version.Family Assessment Device (FAD) [53] – can be filled in from 12 -years -old onward. The same items will be used for both parent and child.

Measures were selected based on relevance, satisfying psychometric properties, brevity, and availability in the Norwegian language.

To assess both children’s and parents’ perspectives on the help and support they received following the death, we developed a self -report measure to relate their perception of SEIB and/or care as usual throughout their participation (Help Questionnaire).

As shown in Textbox 4, the families will be assessed at 4 time-points: baseline (T1), and after 3- (T2), 6- (T3), and 9-months (T4) follow-up. T1 will just comprise the use of two questionnaires: GHQ-12/SDQ and IES-R/CRIES-8. Given the closeness in time of T1 to the death, we expect the families to be acutely distressed at this time. Apart from T1, all the above-mentioned parent and child questionnaires will be included at the other time-points for assessment. These questionnaires will provide useful information on future power calculations and possible SEIB outcomes.

Assessment time-points and measures for all participants.T1: BaselineSociodemographicsParent: IES-R; GHQ-12Child: CRIES-8; SDQT2: 3 monthsHelp QuestionnaireParent: IES-R; ICG-19; GHQ-12; WSAS; CSS; PCS; APQ; FADChild: CRIES-8; IPG-A; SDQ; APQ; FADT3: 6 monthsSame as T2T4: 9 monthsSame as T2

We will inspect data on the flow of participants throughout the trial in order to estimate recruitment and final retention rates. Partial retention rates for those entering the trial who do not complete questionnaires at 9-months follow-up will also be calculated. Besides, the psychologists will inform the research team about the number of attended sessions and reasons for dropping out treatment.

To assess recruitment materials and procedures we developed a brief questionnaire that will be sent to the recruiting agencies at the end of the recruitment phase. The usefulness of randomization and data collection materials (eg, sealed opaque envelopes, informed consent forms, questionnaires) will be evaluated by the researcher who will fill in a ‘brief family log’ after visiting the family.

### Sample Size and Statistical Analyzes

In light of the small state of knowledge about early intervention in the aftermath of a potential traumatic death of a partner/parent, this study is not aimed to test SEIB effectiveness. Power analysis is not used to determine the final sample size, because it is not recommended for pilot studies that do not rely on inferential statistical tests [57]. Following a general rule of thumb that suggests the inclusion of 30 participants or more to determine a parameter (eg, mean/standard deviation) of an outcome variable [58], we will recruit a total of 60 families (30 families in each group). Rather than focusing on hypothesis testing, this pilot study builds on the practical limitations of recruitment and topics of incertitude, such as the need to gather initial estimations for sample size calculation [57,59,60].

Statistical analyzes will be computed using IBM SPSS Statistics and multiple imputation methods will be used to impute values of missing data [61]. Descriptive data will be computed to characterize the sample. On the basis that pilot study analyzes should be mostly descriptive and should provide confidence interval estimation [60,62], descriptive statistics (including mean, percent, standard deviation, and range), and confidence intervals will be used to describe all outcome variables at T1, T2, T3, and T4 providing important information regarding recruitment and randomization procedures, data collection forms, retention rates, future power calculations, and SEIB most appropriate outcomes.

Given the acknowledged low power of pilot studies [57], an emphasis will be placed on evaluating indices of clinical significance. Independent of the normal distribution and sample size, the effect size estimation has been considered a strong predictor of clinically meaningful change in studies with small sample sizes [63]. Accordingly, Cohen’s *d* effect size of the differences in outcomes between groups and Cohen’s *d* effect size of change from baseline to follow-up will be performed and judged as follows: small (*d* ≥ 0.2), moderate (*d* ≥ 0.5), large (*d* ≥ 0.8), or very large (*d* ≥ 1.3) [64]. The preliminary early effects of SEIB will be addressed by comparing descriptive data and effect sizes at T2 of both immediate-SEIB group and delayed-SEIB group (receiving care as usual at T2). The preliminary effects of both immediate and delayed SEIB versions will be addressed by comparing descriptive data and effect sizes of the immediate-SEIB group at T2 and T3 to the delayed-SEIB group at T3 and T4.

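### Cohen's d is graded by its point value as an index of clinical significance, on the premise that sample size does not matter; at 30 families per arm the grades are too imprecise for that use

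*Protocol article*

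**What the plan says.** All of this is in the protocol article, Methods, Sample Size and Statistical Analyzes.

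- **Size.** "we will recruit a total of 60 families (30 families in each group"). The basis is a rule of thumb for estimating a parameter such as a mean or SD, and "Power analysis is not used to determine the final sample size".
- **Emphasis.** "Given the acknowledged low power of pilot studies [57], an emphasis will be placed on evaluating indices of clinical significance".
- **Premise.** "Independent of the normal distribution and sample size, the effect size estimation has been considered a strong predictor of clinically meaningful change". The sentence ends by referring to small studies and cites a source.
- **Rule.** As a stated consequence, between-group d and d for change from baseline are "judged as follows: small (*d* ≥ 0.2), moderate (*d* ≥ 0.5), large (*d* ≥ 0.8), or very large (*d* ≥ 1.3"). The rule is applied to d itself and carries no condition on precision.
- **Use.** SEIB's early effects are addressed by comparing descriptive data and effect sizes between the arms at T2. The immediate and delayed versions are compared in the same way, with T2 and T3 of one arm set against T3 and T4 of the other.
- **Intervals.** Confidence intervals are planned for the outcome variables at T1 to T4. They are not mentioned for d or for the grades.

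**The concern.** The argument in the text is that power is low, so the analysis should turn to effect sizes, which are taken to be meaningful whatever the sample size. But low power and an imprecise d have the same cause, a small n. Grading the point estimate does not avoid the problem; it only stops showing it.

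There is a second difficulty. Cohen's d divides a mean difference by the sample SD. It makes no reference to a change on the IES-R, ICG-19 or any other instrument that a patient or clinician would regard as important, so it is not by itself an index of clinical significance.

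If the plan is followed as written, chance differences can be reported as clinically graded effects of SEIB, in a pilot that says it does not test effectiveness.

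**Working it through.** **The plan's own figure.** 30 families per group × 2 groups = 60. No alpha, power, SD or effect size enters, so there is no power formula to reproduce.

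**Inputs.** n = 30 per arm and cut-offs 0.2, 0.5, 0.8, 1.3 (Sample Size and Statistical Analyzes); 8 parent measures at T2 (Outcome Measures, Textbox 4). Assumptions: independent families, normal outcomes, one parent respondent per family, one score per measure. The documents give no correlation between measures, so a range is used.

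**Step 1: sampling error of between-group d.** With no true effect, SE = √(2/n) = √(2/30) = 0.258. The 95% half-width is t(0.975; 58 df) × 0.258 = 0.517. Adjacent cut-offs lie 0.3, 0.3 and 0.5 apart.

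Exact 95% intervals around an observed d (noncentral t, 58 df):

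| Observed d | 95% CI |
|---|---|
| 0.2 | −0.31 to 0.71 |
| 0.5 | −0.02 to 1.01 |
| 0.8 | 0.27 to 1.32 |

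A d exactly at the threshold for *small* or for *moderate* is therefore compatible with no effect.

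**Step 2: chance of a grade when the true effect is zero.** d/√(2/n) follows t with 2n − 2 df, so P(|d| ≥ c) = 2·P(t > c/√(2/n)).

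| Cut-off c | c/0.258 | Either direction | In SEIB's favour |
|---|---|---|---|
| 0.2 | 0.775 | 44.2% | 22.1% |
| 0.5 | 1.936 | 5.8% | 2.9% |
| 0.8 | 3.098 | 0.3% | 0.15% |
| 1.3 | 5.035 | about 0 | about 0 |

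**Step 3: dependence on n.** The same formula at smaller arm sizes (assumed, for example after loss to follow-up):

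| n per arm | P(\|d\| ≥ 0.2) | P(\|d\| ≥ 0.5) |
|---|---|---|
| 30 | 44% | 6% |
| 24 | 49% | 9% |
| 20 | 53% | 12% |
| 15 | 59% | 18% |

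For P(|d| ≥ 0.2) to fall to 5% with no true effect, about 2 × (1.96/0.2)² = 192 per arm would be needed.

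**Step 4: eight parent measures at T2, all null.** The expected number graded *small* or larger is 8 × 0.442 = 3.5. If the measures were independent, the chance of at least one such grade is 1 − (1 − 0.442)⁸ = 99%, and of at least one *moderate* or larger 1 − (1 − 0.0577)⁸ = 38%. Simulation (10,000 runs, equal correlation):

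| Correlation | At least one ≥ 0.2 | At least one ≥ 0.5 |
|---|---|---|
| 0 | 98.9% | 37.8% |
| 0.3 | 98.4% | 33.3% |
| 0.5 | 97.0% | 28.0% |

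No figure is given for child measures, because the documents do not say how many informants aged 12 to 18 each arm will have. None is given for d of change from baseline, because its error depends on a within-person correlation that the documents do not state.

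**The case against.** **It is an exploratory pilot.** The article disclaims effectiveness testing more than once and admits low power in the same paragraph as d. That limits the harm. It does not justify a grading presented as clinical significance; if anything it makes such a grading harder to defend.

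**Intervals are planned, and a condensed article may leave the interval for d to a fuller document.** A missing interval alone would not be a finding. What stands is that the article states a positive rule: grade the point value, for a reason that sets precision aside. The planned intervals do not condition that rule.

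**The population d does not depend on n, and the sentence reports a cited source.** Both are true. But the sentence concerns estimation in small studies and is used to justify the grading. There it is the sampling error that matters.

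**Small to very large are conventional size words, not claims that an effect exists.** This is fair in general. Here they are introduced as indices of clinical significance and are used to address preliminary effects.

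Three stronger readings are tempting, and the documents do not support them:

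- *The plan picks main-trial outcomes or targets from the largest d.* The phrase "future power calculations, and SEIB most appropriate outcomes" belongs to the sentence on descriptive statistics and confidence intervals, before d is introduced. Outcome Measures already anticipates traumatic stress as primary, on theoretical grounds. No section says that selection will follow d.
- *Null outcomes will routinely earn high grades.* For a single outcome this holds only for *small*. *Moderate* occurs in 6% and *large* in 0.3%.
- *d is seriously inflated in small samples.* The correction factor at 58 df is 1 − 3/(4 × 58 − 1) = 0.987, or about 1.3%.

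**Conclusion.** The concern holds. Grading d by its point value and calling it an index of clinical significance, on a premise that removes sample size from consideration, is unsound at 30 per arm. The interval around d spans at least the distance to the next cut-off on either side. A *small* grade carries almost no information: it arises in 44% of null outcomes, 22% in SEIB's favour. A *moderate* grade is uncommon for any one null outcome (6%), but appears somewhere among 8 null parent measures in about 28–38% of trials.

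The single-outcome figures rest on 30 analysed families per arm, independence and normality. The 8-measure figures also rest on an assumed correlation of 0 to 0.5. Smaller arms make all of them worse. The conclusion about the premise needs none of these assumptions. The point should be corrected, but it does not threaten the pilot's feasibility aims.

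**What to change.** In Sample Size and Statistical Analyzes:

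1. Report every between-group d with its 95% confidence interval, beside the raw mean difference on the instrument's own scale.
2. State that conclusions on preliminary effects will be worded from the interval, not from the point label.
3. Remove the statement that effect size indicates clinically meaningful change independent of sample size, and stop describing d as an index of clinical significance.
4. As a precaution, state that neither main-trial target differences nor main-trial outcomes will be chosen from the size of the pilot d. The protocol does not say that they will be, so this only closes a door left open.

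Hedges g may replace d, but at this size that is an optional refinement.

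The cost is one extra column of intervals and more modest wording of the results. No new data are needed and the design does not change.

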## Introduction

Bereavement is a natural and common event, and most people are generally able to adapt to the resulting grief over time and regain function in their everyday life [1]. However, approximately 10% to 22% of bereaved people experience deleterious forms of mental distress that result in mental health deterioration [2]. The loss of a significantly loved person through death can be a complex and disturbing life event that is linked to greater psychological problems, physical illness, and mortality. Individual grief reactions can vary from minor and shorter responses to more severe and prolonged manifestations [3]. More importantly, unnatural and violent deaths significantly cause more severe after effects than natural deaths [4].

Complicated grief encloses the more severe and prolonged symptoms that hamper social and occupational functioning [3,5]. It has been found to be related to higher rates of mental disorders, sleep problems, suicidality, cardiovascular and cancer diseases, and lack of social support [6-10]. Preoccupied thoughts of the deceased, intense searching and yearning for the deceased, avoiding memories of the deceased, death denying, and crying are among the core symptomatology of complicated grief [11]. In addition, other comorbid symptoms that meet the criteria for depression and/or posttraumatic stress disorder (PTSD) have been documented [12].

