### Participants and Eligibility Criteria

The sample will include bereaved families with children younger than 18 -years old, who suddenly and unexpectedly lose a partner and a parent. Bereaved partners and their children, aged from 12 - to 18 -years old, will be the informants of the study. To ensure a homogeneous sample, all family members must speak Norwegian. Eligible families are those who satisfy both of the criteria listed in Textbox 1.

Inclusion criteria.Criterion for unexpectedness: the loss shall occur following an accident, a suicide, a murder, or a disease, as well as situations where people are missing (presumed dead).Criterion for suddenness: the loss shall occur shortly, or within the same day as the event/disease happened or started. This period can be extended up to 5 days for people who do not regain consciousness after the incident (eg, illness/accident/suicide, etc). The families cannot enter this study later than 3 weeks after the death.

Potential participants with severe medical conditions for both bereaved partner and their children, such as serious physical impairment, intellectual deficit, severe child developmental problems, borderline personality disorder, history of psychosis (eg, schizophrenia, bipolar disorder), current substance use disorder (in the past 6 months), severe suicidal risk, or dementia will be excluded. Families receiving concurrent psychotherapeutic intervention for problems concerning loss and/or trauma will also be excluded.

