### Ethical Considerations

The Regional Committee of Research and Ethics in Western Norway (no. 599832) approved the design and procedures of this study. The ethical principles for research in the social sciences and the humanities will follow the Helsinki Declaration guidelines' [65]. From the start, participants’ needs will prevail over research interests. The agreement to participate in the study and an explicit written informed consent will precede data collection. Participants will be informed about all the relevant aspects of the study (eg, aims, methods, allocation, etc). They will also be reassured that their participation is voluntary and that they can withdraw at any time without detriment. The participant’s privacy and confidentiality will be assured throughout all research phases. Both researchers and psychologists will monitor potential adverse effects or special circumstances that will require participants’ removal from SEIB. Additionally, all participants can make use of care as usual, which seems particularly significant to those in the control condition who are waiting for the delayed SEIB program.

The participant’s informed consent will be obtained shortly after the death. However, several researchers have underlined the difference between being distressed, and not being capable of making decisions around enrollment in a bereavement research study [66,67]. In fact, bereaved people are often involved in complex decision-makings concerning the funeral planning, their financial situation, and so on. Besides, they do not report their research participation as undue strain [68]. Acknowledging a temporary distress, they emphasize their research participation as positive, without showing regrets, and highlight the benefits of participation when they are being respectfully, sensitively and properly cared for [68]. Nevertheless, given the closeness of T1 to the death, where the families may be acute distressed/disturbed, it is necessary to limit the potential strain that can be added to the families. Presenting many questions to the family members at this early time following the loss may lead to problems or even discourage their retention in the study. In addition, their diminished cognitive resources may negatively affect their ability to properly fill in many questionnaires at this time. Therefore, T1 will just comprise the use of the above -mentioned 2 questionnaires.

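### Within-arm change from a baseline taken just after the death is graded as clinical significance, so natural recovery alone can earn the grade, and in the time-shifted aim 6 comparison it does not cancel

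*Protocol article*

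**What the plan says.** Under Sample Size and Statistical Analyzes, the article states that "an emphasis will be placed on evaluating indices of clinical significance". It gives as its reason that "the effect size estimation has been considered a strong predictor of clinically meaningful change in studies with small sample sizes". It then plans two effect sizes: Cohen's d between groups, and Cohen's d of change within a group. On the second it says that Cohen's d "effect size of change from baseline to follow-up will be performed and judged as follows: small" from 0.2, moderate from 0.5, large from 0.8 and very large from 1.3. Both share one scale and one label.

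On the baseline, Participants and Eligibility Criteria says: "The families cannot enter this study later than 3 weeks after the death". Outcome Measures adds: "Given the closeness in time of T1 to the death, we expect the families to be acutely distressed at this time". On the natural course, the Introduction says that "most people are generally able to adapt to the resulting grief over time and regain function in their everyday life".

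Only IES-R and GHQ-12 (parent) and CRIES-8 and SDQ (child) are collected at T1. The delayed arm starts SEIB 3 months after the loss (Trial Design), and the analysis section describes it as on care as usual at T2. Early effects (aim 5) are read by comparing the two arms at T2. The two versions of SEIB (aim 6) are compared by setting the immediate arm at T2 and T3 against the delayed arm at T3 and T4.

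**The concern.** A change score that starts in the first days or weeks after a sudden death contains whatever recovery would have happened anyway. The plan does not separate that part from an effect of SEIB before attaching a verbal grade and calling it clinical significance. The delayed arm shows the difficulty most plainly: its T1 to T2 change precedes SEIB, yet it is graded on the same scale under the same label. IES-R and CRIES-8 measure traumatic stress, the anticipated primary outcome, so the grade falls on the measures that matter most.

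What is at stake is the conclusion the pilot may draw. A moderate or large within-arm d can be read as a sign that SEIB helps when it may only describe the passage of time. In aim 6, the version of SEIB measured later after the loss is credited with the additional recovery.

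**Working it through.** **The plan's own figure.** 2 arms × 30 families = 60, as stated. The article gives no mean, SD, expected fall or T1–T2 correlation, so these are assumptions below and are shown over a range.

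**Set-up.** Take an inert programme, 30 per arm and SD 1 at both times. Let T1 ~ N(0, 1) and T2 = −f + ρ·T1 + √(1 − ρ²)·e, where f is the natural fall in SD units, common to both arms, ρ is the T1–T2 correlation (0.3, 0.5, 0.7) and e is standard normal.

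- Within-arm d = (mean T1 − mean T2) / √[(s₁² + s₂²)/2]. Its target value is f, the natural fall itself.
- Between-arm d at T2 = difference of T2 means / pooled SD. Its target value is f − f = 0.

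**Results** (20,000 simulated trials per setting; ranges are over ρ):

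| Assumed fall f | One arm d ≥ 0.5 | Both arms ≥ 0.5 | Both arms ≥ 0.8 | Mean between-arm d at T2 |
|---|---|---|---|---|
| 0.2 SD | 2–9% | 0–1% | 0% | 0.00 |
| 0.3 SD | 10–18% | 1–3% | 0% | 0.00 |
| 0.5 SD | 50–51% | 25–26% | 0–1% | 0.00 |
| 0.8 SD | 91–98% | 83–95% | 25–26% | 0.00 |
| 1.0 SD | 99–100% | 98–100% | 66–79% | 0.00 |

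**Hand check at ρ = 0.5.** The standard error of within-arm d is roughly √[2(1 − ρ)/30] = √(1/30) = 0.183. For f = 0.8, P(d ≥ 0.5) ≈ Φ(0.3/0.183) = Φ(1.64) ≈ 0.95, and both arms 0.95² ≈ 0.90; the simulation gives 0.89. For f = 0.5, each arm has about an even chance, and 0.5² = 0.25.

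**Choice of denominator.** If change is divided by the SD of the change instead, the target is f/√[2(1 − ρ)]. At f = 0.5, both arms then reach 0.5 in 12% (ρ = 0.3) to 61% (ρ = 0.7) of trials. The grade depends on this choice as well.

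**Aim 5.** The common fall cancels at T2. Under no effect, |between-arm d| ≥ 0.5 occurs by chance in about 6% of trials. The 95% half-width is about 1.96 × √(2/30) = 0.51.

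**Aim 6.** Write f(t) for the natural fall at t months after T1. If the compared effect sizes are changes from T1, an inert programme gives:

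- immediate at T2 versus delayed at T3: f(3) versus f(6), a gap of f(6) − f(3);
- immediate at T3 versus delayed at T4: f(6) versus f(9), a gap of f(9) − f(6).

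With assumed values f(3) = 0.5 and f(6) = 0.8, the first pair reads moderate against large, a false advantage of 0.8 − 0.5 = 0.3 SD for delay. Comparing raw scores at the shifted times leaves the same gap, since randomisation balances T1 but not the extra 3 months.

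**Restarting the delayed arm's change at T2** does not repair this. On the same values the delayed change is 0.8 − 0.5 = 0.3 SD against 0.5 SD for the immediate arm, a false advantage of 0.2 SD the other way.

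**The case against.** The strongest reply is that the plan already protects its main question. Aim 5 is assigned to the randomised comparison at T2, with the delayed arm as the care-as-usual reference, and nothing says that change in a single arm demonstrates an effect. The study disclaims any test of effectiveness and plans no hypothesis tests. Change from T1 cannot be computed for ICG-19, WSAS, CSS, PCS, APQ, FAD or IPG-A. The sentence on adaptation concerns bereavement in general, while the same Introduction says that unnatural and violent deaths have more severe after-effects, so recovery in this sample may be slower.

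Most of this stands, and it rules out three stronger readings.

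- A reader might infer that natural recovery will show as moderate or large in both arms. The article gives no size for it, and at an assumed 0.3 SD both arms would rarely be graded moderate.
- A reader might infer that aim 5 is compromised. It is not, because a common fall cancels.
- A reader might infer that outcomes will be chosen, or the main trial sized, on within-arm d. The article ties those purposes to descriptive statistics and confidence intervals for the outcomes at T1 to T4, not to the change d.

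What the reply does not remove is the grade itself. It carries a clinical-significance label, applies to the primary-outcome measures, and is applied to a delayed-arm change that precedes SEIB. Nor does it answer aim 6, where graded effect sizes are used to address preliminary effects and the compared times differ by 3 months. Declaring a pilot exploratory does not make that contrast interpretable.

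**Conclusion.** The point holds in a limited form. Within-arm d from T1 mixes natural recovery with any SEIB effect, and natural recovery alone can earn a small, moderate or large grade in either arm. How often depends on a fall that the article does not state: both arms at least moderate is unlikely at 0.3 SD, about one in four at 0.5 SD, and likely from 0.8 SD. These figures assume an inert programme, 30 analysed per arm, equal SDs at T1 and T2, and correlations of 0.3 to 0.7.

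The problem is confined to IES-R, GHQ-12, CRIES-8 and SDQ. It matters most for aim 6, because the extra 3 months since loss in the delayed arm do not cancel. The article does not say outright that the effect sizes compared there are changes from T1; that is the natural reading of an effect size belonging to one group at one time. This is worth correcting before analysis, since it alters what the pilot may conclude.

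**What to change.** In Sample Size and Statistical Analyzes:

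1. Report within-arm change from T1 with a confidence interval as description only. Remove the small-to-very-large grade and the clinical-significance label from it.
2. Base statements about SEIB's effect on the between-arm difference at the same time since loss: T2 for SEIB versus care as usual, T3 and T4 for immediate versus delayed allocation. Adjust for the T1 value where it was collected, and give the confidence interval.
3. Keep the shifted aim 6 comparison if wanted, but present it as descriptive and confounded with time since loss.
4. Do not compare a delayed-arm change starting at T2 with an immediate-arm change starting at T1 as if they were equivalent.

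The cost is wording and a small change of analysis, with no new data. The reported effects will look less favourable. Aim 6 is answered more cautiously, because T3 and T4 compare the two allocation policies and not the two versions at matched points in their delivery.
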